## Abstract

**Background:**

Suhexiang (SHX) pill is widely used for treating acute ischemic stroke (AIS). Experimental and randomized controlled trials suggested that SHX pill was beneficial for patients with AIS. However, the effectiveness of SHX pill in real-world practice setting remains unclear. It is of great importance to investigate the effectiveness and safety of SHX pill in patients with acute ischemic stroke in real-world clinical practice with long-term follow-up.

**Methods:**

The Suhexiang pill for acute ischemic stroke in Real-world Practice Setting (SUNRISE) is a multicenter, prospective, product-specific, observational study designed to provide insight into the administration of SHX pill for patients with AIS in the real-world clinical practice setting, with an initial sample size of 1000. Eligible patients treated with SHX pill within seven days of AIS onset will be consecutively included in this registry. The primary outcome is the proportion of patients independent at 3 months after stroke onset defined by an mRS score of 0, 1, or 2.

**Conclusion:**

The findings of the SUNRISE registry will not only provide insights into the characteristics of patients who may benefit from SHX treatment, but also may enable the individualized treatment decision-making of SHX pill in real-world practice setting.

**Study registration:**

This study was registered with the ClinicalTrials.gov (URL: https://clinicaltrials.gov/, Unique identifier: NCT05833932).

**Supplementary Information:**

The online version contains supplementary material available at 10.1186/s12906-025-04762-9.

## Introduction

Stroke is one of the leading causes of death and long-term disability in adults worldwide [1, 2]. Globally, the estimated lifetime risk of stroke over the next 25 years is highest in China [3]. A recent cross-sectional study based on a nationally representative survey reported that in 2020, the estimated overall prevalence, incidence, and mortality rate of stroke were 2.6%, 505.2 per 100 000 person-years, and 343.4 per 100 000 person-years, respectively, which indicated approximate 17.8 million cases of stroke, 3.4 million new strokes, and 2.3 million stroke-related deaths in China [4]. A significant financial burden results from stroke-related treatment, post-stroke rehabilitation, and care. It has been reported that China bears the highest economic cost related to stroke globally [5]. The majority of strokes are ischemic due to reduced or blocked blood flow, generally resulting from arterial occlusion, which accounts for 70–83% of all stroke cases in China [6].

Despite substantial advances in reperfusion therapy for acute ischemic stroke during the past decades, only a minority of highly selected patients could receive thrombolytic therapy due to strict criteria. A cross-sectional study of 938 tertiary hospitals and 786 secondary hospitals from 31 provinces in China reported that the overall intravenous thrombolysis for AIS was 5.64%, and the endovascular therapy rate was 1.45%, respectively, indicating that the majority of patients with AIS were not eligible for reperfusion treatments [7]. For those patients who have not received reperfusion therapy, the lack of effective and widely applicable or accessible therapeutic treatments for AIS has resulted in an increasing interest in traditional Chinese medicine (TCM) [8–10].

Suhexiang (SHX) pill is a well-known Chinese patent medicine, mainly manufactured by Lei Yun Shang Pharmaceutical Group Co., Ltd, which has been approved by the National Medical Products Administration of China (approval number: Z32020480) for the treatment of stroke, seizures, infantile convulsion, sudden loss of consciousness, and other dysfunctions [11]. Experimental studies reported that SHX could significantly improve long-term neurological outcomes in the focal stroke model of rats and exert the inhibition of acute proinflammation activation [12]. Meanwhile, SHX pill exerts antiepileptic and anticonvulsant effects, modulating neurotransmitter imbalance and suppressing the central nervous system by increasing the inhibitory neurotransmitter γ-aminobutyric acid (GABA) and inhibiting the excitatory neurotransmitter glutamate [13–15]. In addition, SHX pill confers a therapeutic potential to AD-like pathology of Aβ42 overexpressing Drosophila model via suppression of the hyperactivation of JNK activity and apoptosis, as well as a potential as a therapeutic drug for the treatment of AD and Parkinson’s disease [16–18]. Moreover, several randomized controlled trials (RCTs) suggested that SHX pill combined with conventional treatments showed beneficial effects on neurological function compared with conventional therapy alone [19, 20]. For instance, Yang et al. reported a randomized controlled trial with 98 patients of acute ischemic stroke, in which SHX combined with clopidogrel produced significant improvement of the National Institute of Health Stroke Scale (NIHSS) compared with clopidogrel alone (6.79 ± 2.01 vs. 4.66 ± 1.73, *P* < 0.05) [19].

Despite the promising findings from experimental and clinical trials, the effectiveness of SHX pill in real-world practice setting remains unclear, which has limited its optimal usage in routine practice. It is of great importance to investigate the epidemiology and clinical characteristics of patients who received SHX treatments. Because the RCTs only included highly selected patients with AIS and excluded special populations such as elderly patients, critically ill patients or patients with complicated comorbidities, resulting in little evidence regarding the effectiveness and safety of SHX in these populations. The generalizability of findings from RCTs remains unknown, therefore, these results should be interpreted with caution before more data from real-world clinical practice are available.

The primary objective of the Suhexiang pill for acute ischemic stroke in real-world practice setting (SUNRISE) registry is to evaluate the effectiveness and safety of SHX pill in patients with acute ischemic stroke in routine clinical practice with a one-year follow-up.

## Methods and design

### Study design

The SUNERISE registry is a multicenter, prospective, product-specific, observational study designed to provide insight into the administration of SHX pill for patients with AIS in the real-world clinical practice setting. Physicians decide whether to prescribe SHX pill based on their assessment of the patient’s overall condition, the drug’s stated indications, clinical guidelines, and the patient’s preferences. This present registry is one of the cohorts in the China Stroke Registry for Patients with Traditional Chinese Medicine (CASES-TCM), which is a prospective, multicenter, observational disease-specific registry [21]. Recruitment began on May 1, 2023, and the registry is scheduled to complete recruitment of all human participants by December 31, 2024. The SUNRISE registry has been approved by the Institutional Review Board of Dongzhimen Hospital, Beijing University of Chinese Medicine, Beijing, China (No. 2022DZMEC-268-02), as well as the local ethical committees of all participating sites.

### Study population

Patients will be included in the SUNRISE registry if they meet all the inclusion and none of the exclusion criteria:

#### Inclusion criteria

All adult patients (≥ 18 years of age) admitted to the participating hospitals with a diagnosis of acute ischemic stroke.Acute ischemic stroke within seven days of symptom onset.Treated with Suhexiang pill.Patient or legally authorized representative has signed written informed consent.

#### Exclusion criteria

Known to be allergic to Suhexiang pill or related ingredients.Comorbidities such as severe cognitive impairment, aphasia, or osteoarthritis that may significantly affect the outcomes assessment including neurological function and activities of daily living.Known to be pregnant or breastfeeding.

Importantly, patients are still eligible to participate in this registry if they were previously treated with SHX pill for another condition before the stroke.

### Treatments

SHX pill contains fifteen Chinese herbal medicines [14]: *Styrax* (Su Hexiang), *Benzoinum* (An Xixiang), *Borneolum Syntheticum* (Bing Pian), *Cornu Bubali* (Shui Niujiao), *Moschus* (She Xiang), *Santalum album Linn.* (Tan Xiang), *Aquilariae Lignum Resinatum* (Chen Xiang), *Syzygium aromaticum* (Ding Xiang), *Cyperi Rhizoma* (Xiang Fu), *Radix Aucklandiae* (Mu Xiang), *Boswellia sacra* (Ru Xiang), *Piper longum Linn.* (Bi Ba), *Rhizoma Atractylodis Macrocephatae* (Bai Zhu), *Frctus Terminaliae Chebulae* (He Zirou) and *Cinnabaris* (Zhu Sha). SHX is recommended to be taken orally, with the dosage of one or two pills, one or twice a day, for at least seven days. However, the actual dosage and treatment course of SHX pill will be determined at the discretion of the treating physician as well as the discussion between the patients and the physician. In addition, all participants are allowed to receive routine stroke care in accordance with the guidelines [22], including (but not limited to) intravenous thrombolysis, endovascular treatment, antiplatelet, blood pressure control, as well as management of other risk factors. All the prescribed treatments will be recorded in a standardized electronic case report form (eCRF).

### Data collection and management

Eligible patients will be consecutively screened and included in the SUNRISE registry. All data will be collected via a real-time online data entry system with a predefined eCRF designed for this registry. Baseline characteristics including demographics, medical history, vital signs, the Glasgow Coma Scale (GCS) [23], the National Institutes of Health Stroke Scale (NIHSS) [24], the modified Rankin Scale (mRS) [25], the Barthel Index (BI) [26], Diagnostic Scale of Syndrome Elements in Ischemic Stroke (DSSEIS) [27], pictures of tongue, time of stroke onset, stroke subtypes, and laboratory test, will be collected accurately by investigators in each site. In addition, the details of the SHX treatments and the prescribing information of the treating physician will be documented. Several approaches will be used to minimize the potential heterogeneity or inaccuracy of data according to guidelines [28, 29]. Briefly, investigators from all sites will be trained before enrollment to understand the study protocol and will be required to comply with the standard operation procedure. Furthermore, an independent monitoring group will be responsible for reviewing the eCRFs for data quality. We will assign professionals to review data quality through a combination of online and on-site monitoring, including the timeliness, completeness, accuracy and authenticity of data records. Online data monitoring will be completed instantly, and we will require data revisions to be completed within seven days. Additionally, regular on-site monitoring will be conducted and monthly monitoring reports will be issued.

### Follow-up and study outcome

Local investigators at each site will conduct face-to-face or telephone follow-ups at 3 months (± 7 days), 6 months (± 10 days), and 12 months (± 14 days). An overall schedule of study-related visit and data collection of this registry is shown in Table 1. Briefly, data collection during the follow-up includes: (1) the mRS score will be assessed at 3, 6 and 12 months; (2) the Mini-Mental State Exam (MMSE) [30] will also be assessed at 3, 6 and 12 months; (3) the major events including death, ischemic stroke, intracerebral hemorrhage, myocardial infarction, heart failure and bleeding will be recorded during the follow-up period; (4) Adherence to the SHX treatment will be documented throughout the registry period.

**Table 1 Tab1:** Schedule of study-related activities

	STUDY PERIOD				
	Baseline	Discharge	Follow-up		
Timepoint	T_0_	T_1_	T_2_ (3 months)	T_3_ (6 months)	T_4_ (12 months)
**Enrollment**					
Eligibility screen	**×**				
Informed consent	**×**				
Demographics	**×**				
Medical history	**×**				
Physical examination	**×**				
Neurological evaluation	**×**				
Previous medication	**×**				
CT/MRI	**×**				
ECG	**×**				
Laboratory examination	**×**				
Stroke subtypes		**×**			
Medications		**×**	**×**	**×**	**×**
**Assessments**					
NIHSS	**×**	**×**			
GCS	**×**	**×**			
mRS	**×**	**×**	**×**	**×**	**×**
BI	**×**	**×**			
MMSE			**×**	**×**	**×**
PRO		**×**			
TCM Syndrome	**×**	**×**			
Major vascular events		**×**	**×**	**×**	**×**
Overall mortality		**×**	**×**	**×**	**×**
Complications		**×**	**×**	**×**	**×**

**Abbreviations**: CT, Computed tomography scan; MRI, Magnetic resonance imaging; ECG, electrocardiogram; NIHSS, National Institutes of Health Stroke Scale; GCS, Glasgow Coma Scale; mRS, modified Rankin Scale; BI, Barthel Index; MMSE, Mini-Mental State Exam; PRO, Patient report outcome scale of stroke; TCM, Traditional Chinese Medicine

The primary outcome of the SUNRISE registry is the proportion of patients independent at 3 months after stroke onset defined by an mRS score of 0, 1, or 2. Secondary outcomes include the mRS score at 6 and 12 months; the change of NIHSS score from baseline to discharge; the BI score at discharge; the MMSE score at 3, 6, and 12 months; the GCS score at discharge, the proportion of patients reported major events of interest.

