### Statistical analysis

The SUNRISE registry will be implemented in stages due to time and budget constraints. Aiming to initially gather data on acute ischemic stroke patients treated with SHX, describe and analyze the effects of SHX in real-world practice setting, and provide dependable data support for sample size calculation and protocol design in subsequent phases, the first phase is exploratory and has a target number of 1,000 participants. The next phases of this registry will be determined after the first phase of 1000 participants are completed. Baseline characteristics will be described using standard statistics. All baseline variables will be summarized using means and SDs for continuous variables that were normally distributed, while categorical variables were expressed as absolute frequencies and percentages. Given that the SUNRISE registry is one of the cohorts in the disease-specific CASES-TCM registry, a control group will be selected from the CASES-TCM population using a propensity score matching (PSM) approach to compare the effectiveness of SHX pill for acute ischemic stroke with those not receiving SHX treatment. The PSM will be performed with demographic and baseline characteristics. In each cohort, participants will be matched 1:1 based on propensity scores generated by logistic regression, using the nearest neighbor technique without replacement, with a maximum aperture of 0.2. After PSM, the comparability of outcomes between SUNRISE cohort and CASES-TCM cohort will be performed using a 2-sample t-test, one-way analysis of variance (ANOVA), or nonparametric tests (the $$\:{\chi\:}^{2}$$ test, Fisher’s exact test, or Mann-Whitney U test) as appropriate. Statistical analyses will be done using R software, version 4.1.2. Two-sided P values of less than 0.05 were accepted as statistically significant. A repeated measures analysis of variance (ANOVA) or mixed regression model will be used for repeated measurement data. To measure the relationships between multidimensional variables and outcomes of interest, multivariate regression analysis will be used in this study.

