In addition, missing data are of great importance in real-world studies, in which missing data may cause seriously compromised inferences to scientific credibility of causal conclusion. Hence, we filled in the missing data using multiple imputations with predictive mean matching to ensure data integrity and comparability [31]. Moreover, in this real-world registry, potential confounding factors such as age, sex, smoking, body mass index, and severity of stroke, could be addressed in several ways [32]. The PSM approach will be used for the adjustment of measured confounders to ensure the balance between groups.

Pre-defined subgroup analyses will be performed of the effect of SHX at 3 months, subdivided by age, sex, severity of stroke, type of stroke, and TCM syndrome or TCM symptom.

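### After matching, NIHSS change and discharge BI and GCS are compared with tests that carry no covariate; adding each scale's recorded baseline value would tighten the intervals

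*Protocol article*

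**What the plan says.** In the Protocol article, the paragraph after Table 1 under Follow-up and study outcome gives the discharge-based secondary outcomes: "the change of NIHSS score from baseline to discharge; the BI score at discharge", and then "the GCS score at discharge, the proportion of patients reported major events of interest". NIHSS therefore uses its baseline by subtraction, while BI and GCS are taken at discharge alone.

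Table 1 marks NIHSS, GCS and BI at both baseline and discharge. Data collection and management confirms the baseline measurements: "Baseline characteristics including demographics, medical history, vital signs, the Glasgow Coma Scale (GCS", continuing in the same list to NIHSS and to "the modified Rankin Scale (mRS) [25], the Barthel Index (BI) [26".

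Statistical analysis describes 1:1 nearest-neighbour propensity matching to CASES-TCM controls. On the matching variables it says "The PSM will be performed with demographic and baseline characteristics". The comparison of outcomes between the two cohorts "will be performed using a 2-sample t-test, one-way analysis of variance (ANOVA), or nonparametric tests", the last group being chi-square, Fisher and Mann-Whitney tests, as appropriate. No covariate is mentioned for any of them. The section also plans a repeated-measures ANOVA or mixed model for repeated data and a multivariate regression, without saying which outcomes or covariates these take.

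**The concern.** Three scales share one measurement schedule, and each has a baseline value likely to predict its discharge value. A two-sample test on the discharge score, or on the change, does not make the best use of that value. Two things follow.

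- **Precision.** The test's standard error comes from the full spread of the outcome, including the part that the baseline would explain. Good balance of group means does not remove that part.
- **Residual imbalance.** If matching leaves a baseline difference, the discharge score passes on part of it and the change score over-corrects for it. Neither removes it.

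The first phase is meant to supply data for sizing later phases. Outcome variances estimated without baseline adjustment and carried into that calculation would ask for more patients than an adjusted analysis needs.

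**Working it through.** **Inputs.** From the article: NIHSS analysed as change, BI and GCS as discharge values, all three measured at baseline, 1:1 matching, and a target of 1,000 SHX patients. The article gives no SD, effect size, power or baseline-discharge correlation, so there is no stated figure to reproduce. Assumed: equal SDs at baseline and discharge, a linear relation, and a correlation r of 0.4 to 0.8.

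**Precision.** Relative variance of the treatment comparison, with the discharge score alone set to 1:

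- discharge score: 1
- change score: 2(1 − r)
- baseline-adjusted (ANCOVA): 1 − r²

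The interval narrows by 1 − √(ratio of variances). The sample needed without adjustment, relative to that with it, is the inverse of the same ratio.

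| r | Change | Adjusted | BI, GCS: CI narrower by | BI, GCS: sample ratio | NIHSS: CI narrower by | NIHSS: sample ratio |
|---|---|---|---|---|---|---|
| 0.4 | 1.20 | 0.84 | 8% | 1.19 | 16% | 1.43 |
| 0.6 | 0.80 | 0.64 | 20% | 1.56 | 11% | 1.25 |
| 0.8 | 0.40 | 0.36 | 40% | 2.78 | 5% | 1.11 |

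At r = 0.6, for example, BI and GCS give 1 − √0.64 = 0.20 and 1/0.64 = 1.56. NIHSS gives 0.64/0.80 = 0.80, so 1 − √0.80 = 0.11 and 1/0.80 = 1.25.

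As an illustration, take a true difference of 0.1 SD of the discharge score, 1,000 patients per group (all SHX patients matched), two-sided 5% and r = 0.6. Power is about 61% for the discharge score, 70% for the change score and 80% with baseline adjustment.

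**Residual imbalance.** For a baseline difference of 0.1 SD left after matching, the discharge comparison shifts by 0.1r, that is 0.04 to 0.08 SD for r = 0.4 to 0.8. The change comparison shifts by 0.1(r − 1), that is −0.06 to −0.02 SD.

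How much is left depends on the matching. A small simulation of greedy 1:1 matching without replacement assumed a 0.5 SD baseline difference before matching and 1,000 to 5,000 controls. The mean residual difference was:

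- 0.002 to 0.004 SD with the score in the propensity model and the caliper read as 0.2 SD of the logit
- 0.18 SD (1,000 controls), 0.04 SD (2,000) and about 0.00 SD (5,000) with the score in the model and 0.2 read as a raw probability
- about 0.5 SD with the score left out of the model

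**The case against.** The strongest reply is that baseline adjustment is already planned, through the matching. The score uses baseline characteristics, and Data collection and management lists NIHSS, GCS and BI among them. Statistical analysis also names confounders, "potential confounding factors such as age, sex, smoking, body mass index, and severity of stroke, could be addressed in several ways", and gives matching as the adjustment for measured ones. A reader might infer that these outcomes are compared with no regard to baseline, or that the estimates are biased. The documents support neither. A two-sample comparison needs balance in group averages, which matching targets, and under the usual logit reading of the caliper the simulated residual was negligible. Larger residuals need a raw-probability caliper with a small control pool, or a propensity model without the score. The article establishes neither. The bias part is therefore conditional. The precision part stands, because balanced means do not shrink the standard error of an unpaired test.

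A second reply is that the mixed model and the multivariate regression could carry baseline values. They could, but the text does not assign them to this comparison; it assigns the listed tests. A full analysis plan may settle this.

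Third, these are secondary outcomes in an exploratory phase with no power claim, and an unadjusted test after matching is valid. That limits the weight of the point.

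A reader might also extend the criticism to the primary outcome, mRS 0–2 at 3 months. The same test list covers it, but the figures here concern continuous scores, and no gain has been worked out for a binary outcome.

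**Conclusion.** The point holds as one of efficiency. The tests named for the matched comparison leave out baseline values that the registry collects, and regression on them would give intervals roughly 8% to 40% narrower for BI and GCS and 16% to 5% narrower for NIHSS as r rises from 0.4 to 0.8. This rests on an assumed correlation, equal SDs and a linear relation. BI and GCS in particular are bounded, so the figures are a guide only. Adjustment would also guard against imbalance that survives matching, but the article does not show that any will.

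**What to change.** In the matched set, compare discharge NIHSS, BI and GCS by regression on treatment and the same scale's baseline value, plus age and baseline NIHSS. Use ANCOVA, or an ordinal model where the scores are skewed. Keep the unadjusted tests as supportive. The NIHSS outcome need not be redefined: in a linear model with baseline NIHSS as a covariate, change and discharge score give the same treatment estimate.

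As an optional addition, apply the same kind of covariate adjustment to mRS 0–2 at 3 months, without claiming a particular gain.

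The cost is a few lines in the analysis plan and minor extra analysis work. Every covariate is already collected, and neither the matching nor the visit schedule changes.

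### Major events collected through 12 months are compared as a crude proportion, so unequal loss to follow-up can create a spurious difference between SHX patients and matched controls

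*Protocol article*

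**What the plan says.** Under Follow-up and study outcome, the article states that "the major events including death, ischemic stroke, intracerebral hemorrhage, myocardial infarction, heart failure and bleeding will be recorded during the follow-up period". Contacts are face to face or by telephone at 3, 6 and 12 months, and Table 1 also collects major vascular events and mortality at discharge. The secondary outcome built on these data, given after Table 1, is "the proportion of patients reported major events of interest". It states no time horizon, and it does not say whether the events form a composite or are taken singly.

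Under Statistical analysis, the matched SHX and CASES-TCM groups are to be compared by t-test, ANOVA or nonparametric tests, the last group being chi-square, "Fisher’s exact test, or Mann-Whitney U test) as appropriate". For a proportion, that means chi-square or Fisher. The section also names repeated-measures ANOVA or a mixed model, and a general regression statement: "To measure the relationships between multidimensional variables and outcomes of interest, multivariate regression analysis will be used in this study". No method is described as using time to event or censoring.

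On missing data the article says: "we filled in the missing data using multiple imputations with predictive mean matching to ensure data integrity and comparability". It does not say whether this covers event status after a patient is lost.

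**The concern.** A proportion compared by chi-square or Fisher is sound when every patient is followed to the horizon or dies before it. This registry follows patients for a year through local visits or telephone calls in routine care. Some loss is likely, and the missing-data paragraph itself warns that missing data can compromise causal conclusions.

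A patient last seen event-free at month 4 has contributed four months of information and none after that. A crude proportion cannot represent this. It must treat the patient as event-free for the year, leave the patient out, or fill in a yes or no. If loss differs between the groups, the resulting error does not cancel.

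The stated primary objective covers effectiveness and safety with one-year follow-up, and these events carry much of the safety reading. The first phase is also meant to supply data for sizing later phases, so the absolute risks matter as well as the comparison.

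**Working it through.** The article gives no event rate, loss rate or power for this outcome, so there is no figure to reproduce. What follows is an illustration with assumed rates.

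**Inputs (all assumed).** True 12-month risk F, the same in both groups: 10% or 15%. Loss by 12 months L: 5% in one group and 20% in the other. Event and loss rates are constant and independent.

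**Formulas.** Event rate h = −ln(1−F); loss rate l = −ln(1−L).
- Event seen before loss: A = h/(h+l) × (1 − exp(−(h+l))).
- Followed to 12 months event-free: C = (1−F)(1−L).
- Lost event-free: U = 1 − A − C.
- Lost patients counted as event-free: the estimate is A.
- Lost patients dropped: the estimate is D = A/(A+C).
- Simple imputation, with event status drawn for U at the rate seen in patients of known status: A + U×D. Since A = D(A+C), this equals D(A+C+U) = D, exactly the dropped result.

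**F = 10%** (h = 0.1054).
- L = 5% (l = 0.0513): A = 0.0975, C = 0.8550, U = 0.0475, D = 0.0975/0.9525 = 0.1024.
- L = 20% (l = 0.2231): A = 0.0898, C = 0.7200, U = 0.1902, D = 0.0898/0.8098 = 0.1109.

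**F = 15%** (h = 0.1625).
- L = 5%: A = 0.1463, C = 0.8075, D = 0.1534.
- L = 20%: A = 0.1348, C = 0.6800, D = 0.1655.

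| True risk, both groups | Handling of lost patients | 5% loss | 20% loss | Spurious difference |
|---|---|---|---|---|
| 10% | event-free | 9.8% | 9.0% | −0.8 points |
| 10% | dropped or simply imputed | 10.2% | 11.1% | +0.9 points |
| 15% | event-free | 14.6% | 13.5% | −1.1 points |
| 15% | dropped or simply imputed | 15.3% | 16.5% | +1.2 points |

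**Why simple imputation fails.** To recover the true 10% at 20% loss, patients lost event-free should receive an event with probability (0.1000 − 0.0898)/0.1902 = 5.4%, because they have already passed part of the year safely. Imputation that ignores that time gives them 11.1%.

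**Equal loss.** With 20% loss in both groups and true risks of 10% and 15% (ratio 1.50), the ratio is 13.5/9.0 = 1.50 if lost patients count as event-free and 16.5/11.1 = 1.49 if dropped. The ratio hardly moves, but each absolute risk is shifted.

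**Censoring at last contact.** A simulation of 1,000 runs with n = 1,000 assumed a 10% risk of a non-fatal event and 10% of death, each taken alone, for a true cumulative incidence of 9.5%. At 20% loss the crude proportion averaged 8.6% and the Aalen-Johansen estimate 9.6%. Without loss both gave 9.5%.

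**Effect on the test.** Under those event and death rates, with 1,000 per group and lost patients counted as event-free, 5% versus 20% loss gives about an 8% chance (non-fatal event) or 13% chance (composite with death) of a significant result in the spurious direction, against 2.5% nominal.

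**The case against.** Four points can be made for the plan.

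1. *Competing death.* A reader might infer that the crude proportion is also biased because patients who die early can no longer have a stroke or infarction. The documents do not support this. Planned follow-up has the same length for everyone, and with complete follow-up the crude proportion is the cumulative incidence. At 5% and 15% mortality and the same event rate it is 9.75% and 9.24%: a true difference, to be read beside mortality. Death is also a listed major event, so in a composite it does not compete. This point stands in full.

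2. *Same registry.* A reader might suppose that the two groups are followed under separate registries with different retention. The article makes SUNRISE one of the cohorts within CASES-TCM. Nothing in it shows unequal loss, and the 5% versus 20% contrast is an assumption. This stands, although equal retention is not documented either.

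3. *Multiple imputation is planned.* It could cover event status, but the article does not say that it does. If a 12-month indicator is imputed without using the event-free time already observed, the dropped-patient bias returns.

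4. *A condensed article.* Horizon, denominator and event-date fields may sit in a full protocol or analysis plan that is not shown, and the regression statement does not exclude a Cox model. This lowers the severity. It does not remove the point, because the article does fix the summary measure as a proportion and does name the tests.

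**Conclusion.** The point holds in limited form. The stated measure and tests take no account of when follow-up stopped, and every simple way of handling early loss misestimates the 12-month risk. With unequal loss the comparison acquires a spurious difference of about 0.8 to 1.2 points under the assumed rates. Its sign reverses between counting lost patients as event-free and dropping or simply imputing them. With equal loss the ratio is nearly intact, but the absolute risks are still shifted.

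The size rests on assumed 10% to 15% risks, constant rates, loss unrelated to risk, and 5% versus 20% loss. The 12-month horizon is read from the visit schedule, since the outcome definition gives none. Severity is low to moderate: this is one secondary outcome in a phase described as exploratory, and the article gives no loss figure.

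**What to change.** State the horizon (12 months) and whether the events are analysed as a composite or singly. Use the date of each event and of last contact, with follow-up censored at last contact. Then:

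- For death, or a composite that includes death: Kaplan-Meier estimates at 12 months and a Cox model.
- For non-fatal events taken singly: Aalen-Johansen cumulative incidence with death as the competing event, and cause-specific Cox models, reported beside mortality.
- For both: standard errors clustered on matched pair.
- Report loss to follow-up by group. Do not impute 12-month event indicators without regard to the follow-up already observed.

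This is a cheap improvement: date fields, if the case report form does not already hold them, and standard R code. The drawback is that event dates reported by telephone may be accurate only to the month.
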